##### Resources and barriers

The implementation of volitional skills and goal pursuit are influenced by a variety of factors. There may be barriers and impediments to physical activity, but also support and resources [54]. Beside self-regulatory skills and (exercise) self-efficacy, social support has a high impact on physical activity behaviour. Significant others, such as health care professionals, exercise instructors, family members or friends, may positively influence the initiation and maintenance of a physically active lifestyle [81].

→ Implementation in the intervention: the HOMEfit concept is based upon the structured support given by the GP's practice. The GP recommends and repeatedly encourages his/her patient to take part in the exercise programme. The exercise therapist provides individual consultations to foster patients' motivation and volitional skills to perform the home-based exercise programme.

Beyond this social support, session no. 6 is targeted towards discussing potential support from family members or friends and other resources for overcoming identified barriers to physical activity (see "Coping planning" and Table 3).

##### Materials (experimental intervention)

Each participant gets an illustrated workbook that contains information on each topic of the eight intervention sessions as well as instructions and pictures for all home-based exercises. Additionally, it provides worksheets for goal setting, strategic planning, and action control (activity log).

Participants are equipped with pedometers (Walking style Pro, Omron Healthcare Co., Kyoto, Japan). Furthermore, they receive elastic resistance bands for performing several home exercises (Thera-Band^® ^GmbH, Dornburg-Frickhofen, Germany). Two different levels of resistance, which are rather low within the available range, have been chosen for the HOMEfit programme: yellow ("thin") and red ("medium"). Every participant is provided with one yellow and one red band.

#### Control intervention details

The control intervention focuses on promoting baseline activity. Baseline activities are defined as "light-intensity activities of daily life, such as standing, walking, and lifting lightweight objects" [[57], page 2]. An increase in these activities is not expected to result in the same health benefits brought about by an exercise programme or walking as exercise. However, minor positive effects (due to a reduction of sedentary time and an increase in total energy expenditure) still seem possible, especially in previously sedentary older adults.

##### Consultation sessions

Table 4 presents the eight sessions of the control intervention. The topics discussed in the initial face-to-face consultation are similar to the first session of the experimental intervention. During the second face-to-face session, exercise therapists discuss participants' daily routines with regard to their physical activity and sedentary behaviour. During the final personal consultation, participants once again reflect about their daily routine and current physical activity level compared to the level at the beginning of the study. The two blocks of personal and telephone consultations in between are dedicated to the discussion of opportunities for increasing baseline activity at home and in public, and implementation, respectively. Finally, participants are counselled by phone with regard to staying active in daily life.

**Table 4 T4:** Overview over the 12-week control intervention

**Session no**.	1	2	3	4	5	6	7	8
**Intervention week no**.	1	2	4	5	7	8	11	12

**Type of contact**	face-to-face	face-to-face	face-to-face	by telephone	face-to-face	by telephone	face-to-face	by telephone

**Beginning**	Motives for participation	Identification of state of health and feeling						

**Topics**	Current PA behaviour and exercise biography General health benefits of PA Baseline PA The programme, organisational aspects	My daily routine and physical (in)activity	Opportunities for increasing baseline activity at home	Implementation of baseline activities at home	Opportunities for increasing baseline activity in public	Implementation of baseline activities in public	My daily routine and physical (in)activity: before and today	Staying physically active Falling back into inactive behaviour

PA = physical activity

There is no goal setting or strategic planning in the control intervention. Exercise therapists focus on giving information and instructions.

##### Materials (control intervention)

Each participant receives a booklet containing information on the benefits of physical activity for health and everyday life, opportunities to integrate more baseline physical activity into the daily routine, and on how to keep up. Participants receive no further materials.

### Study data

#### Baseline data

##### Characterisation of participating practices

Profile data of practices are evaluated by a self-report questionnaire completed during the initiation visit to the respective practice (urban or rural area; quarterly number of patients seen; number, age and sex of all involved practitioners). Questionnaires (paper protocols) are forwarded to the data manager.

##### Characterisation of exercise therapists

Date of birth, sex and vocational background (university degree/vocational training) of exercise therapists are evaluated by self-report questionnaire. Questionnaires (paper protocols) are forwarded to the data manager.

##### Characterisation of participants

Baseline data of participants are assessed within the baseline assessment (T0, see Figure 1). Socio-demographic data (including year of birth, sex, socio-economic status, living situation, social support) are assessed by computer-assisted telephone interview following German epidemiologic standards published by the Robert Koch Institute [82]. Physical activity is assessed by the use of the PRISCUS-Physical Activity Questionnaire (PRISCUS-PAQ), administered by telephone interview [83-85]. Current walking ability (no walking aid/cane/rollator) and frequency of falls (12-month recall) are also assessed by telephone interview. Falls are defined as "an unexpected event in which the participants come to rest on the ground, floor, or lower level" [86].

Weight and height are measured by standard protocol at the GP's practice by a trained assessor and electronically documented.

Chronic diseases (according to the inclusion criteria: essential hypertension, non-insulin-dependent diabetes mellitus, chronic ischaemic heart disease, heart failure, atherosclerosis of arteries of extremities, chronic obstructive pulmonary disease, chronic kidney disease, spinal osteochondrosis, coxarthrosis, gonarthrosis, osteoporosis with or without pathological fracture) are documented by the GP on a standardised paper protocol. Finalised protocols are forwarded to the data manager by fax. Originals remain in the practice (for monitoring purposes).

#### Efficacy data

Efficacy data are assessed within the baseline assessment (T0, before randomisation) and within the final assessment (T1, after 12 weeks of intervention, see Figure 1). Data from baseline and final assessment obtained by computer-assisted telephone interview are electronically documented. Data obtained within the motor tests at the GP's practice are documented on a standardised paper protocol. Electronic files and paper protocols are forwarded to the data manager.

##### Primary efficacy endpoint

The "chair-rise" test, a timed test of five maximum speed repetitions of rising from a chair (arms folded across the chest) and sitting down, is considered to be a measure of functional lower body strength and dynamic balance capability and serves as primary outcome (continuous variable) [87-90]. A test-retest (2 weeks) correlation of 0.73 has been reported for this measure [91]. The terms "chair stand" [91] or "sit to stand" [92,93] have also been used for this test.

Rising from a chair without hand use is a complex motor task that is challenging for many elderly individuals, in particular for those who suffer from neuromuscular or musculoskeletal impairments [94-97]. Lower body strength and reduced balance limit mobility (e.g., walking speed, independent ambulation, stair climbing) [92,98-100] and constitute important risk factors for falls [12] in older adults. Prospective cohort studies suggest that measures of lower extremity function may predict the future onset of disability [87,90], hospital [88] and nursing home use [101], and mortality [102].

The test is performed by a specially trained assessor at the GP's practice and is documented on a standard paper protocol. For methodological reasons, patients who are unable to perform the test have to be excluded from participation. Guralnik et al. [90] reported that in a sample of more than 5,000 community-dwelling older adults (71 years and older), 21.6% were unable to complete the test. However, within our feasibility study, only 3 out of 91 participants (3.3%) were unable to perform the test.

##### Secondary efficacy endpoints

Further physical functioning (mobility, aerobic capacity, strength, balance, and flexibility) is assessed by the use of different performance tests. All of these tests are performed by a trained assessor at the GP's practice in a given order. The "timed up-and-go" (TUG) is used to quantify mobility and coordination [103]. The time that the patient needs to rise from a chair, walk three metres, turn, walk back, and sit down again (one attempt) is taken. The test has been shown to be a sensitive and specific measure for identifying elderly individuals who are prone to falls [104]. The "2-minute step-in-place" test is used as a measure of aerobic endurance [105]. This test assesses the number of times, within two minutes, that the participant is able to step in place, raising his/her knees to a height halfway between the iliac crest and the middle of the patella (one attempt). Grip strength of the patient's dominant hand is measured using a Jamar hand dynamometer (Sammons Preston Inc., Bolingbrook, IL, USA) (best of three attempts) [106]. "Tandem stand" is used to assess standing balance. The patient's attempt to maintain his/her feet in the tandem position (heel of one foot directly in front of the other foot) is timed (maximum ten seconds, best of three attempts) [107]. Walking balance is assessed by "tandem walk". Patients are asked to attempt to walk with the heel of one foot directly in front of the other foot (maximum eight steps, best of three attempts). The "chair sit-and-reach" test (one attempt per leg) is used as a measure of hamstring flexibility [108].

Physical activity is estimated by the use of a pedometer (Walking style Pro, Omron Healthcare Co., Kyoto, Japan) and expressed as "mean steps per day". Participants are asked to wear the pedometer for a period of six days.

Health-related quality of life, fall-related self-efficacy ("fear of falling") and exercise self-efficacy are assessed by the use of questionnaires. The Short Form-8 Health Survey (SF-8™ 4-week recall version; computer-assisted telephone interview) that yields an eight-part profile of functional health and well-being is used to assess health-related quality of life. Two SF-8 composite scores are calculated: the SF-8 physical component score (PCS) and the SF-8 mental component score (MCS). The instrument has demonstrated good reliability and validity [109]. Fall-related self-efficacy ("fear of falling") is assessed by the Falls Efficacy Scale-International Version (FES-I; computer-assisted telephone interview) that has demonstrated high internal reliability and high test-retest reliability [110]. The confidence that one is capable of adhering to an exercise programme even under adverse conditions (exercise self-efficacy) is assessed by the "SSA-Scale" (according to Fuchs & Schwarzer [111]; self-administered questionnaire on paper protocols).

All secondary outcome measures result in continuous variables.

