##### Primary efficacy endpoint

The hypothesis of differences between the two groups (experimental vs. control) concerning the post-interventional chair-rise time, is tested using an ANCOVA with chair-rise time at baseline, treatment group and study centre effects as explanatory variables. Analysis of the data is undertaken using the principle of "intention-to-treat" (ITT) which will be used as the official result of the study. Additionally, a secondary "per protocol" analysis is performed. Participants who abort the intervention are not invited for the final assessment. This will result in missing values. Missing values in both groups are each replaced by randomly selecting a change in chair-rise time from the control group and adding this difference to the baseline chair-rise time (see sample size calculation).

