##### Secondary efficacy endpoints

Effects on secondary endpoints are analysed in the same manner as effects on the primary endpoint. Cases with a missing value at baseline are excluded for the respective analysis.

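### The chair-rise imputation, carried over without bounds to tandem stand and tandem walk, can give drop-outs scores above the tests' maxima (minor; two secondary endpoints)

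*Protocol article*

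**What the plan says.** Four statements in the protocol article combine.

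- **The scales.** Under Study data, Secondary efficacy endpoints, tandem stand "is timed (maximum ten seconds, best of three attempts"), and tandem walk is scored with "maximum eight steps, best of three attempts".
- **The scale type.** That section closes with "All secondary outcome measures result in continuous variables", with no exception for capped tests.
- **The analysis rule.** Under Statistical analyses, Secondary efficacy endpoints: "Effects on secondary endpoints are analysed in the same manner as effects on the primary endpoint". The only departure stated is "Cases with a missing value at baseline are excluded for the respective analysis".
- **The rule inherited.** Under Statistical analyses, Primary efficacy endpoint, the comparison "is tested using an ANCOVA with chair-rise time at baseline, treatment group and study centre effects as explanatory variables". For missing data: "Missing values in both groups are each replaced by randomly selecting a change in chair-rise time from the control group", then "adding this difference to the baseline chair-rise time (see sample size calculation").

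The article nowhere limits an imputed value to a test's range, and nowhere matches the control donor to the recipient's baseline.

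**The concern.** For chair-rise time, baseline plus a borrowed change meets no upper limit, because that test has no stated maximum. Tandem stand and tandem walk do have one. A participant already at the maximum has no room to improve, yet the rule can give that person an improvement seen in a control who started lower. The result is a score that no assessor could have recorded. The same thing can happen at zero when a low scorer draws a loss.

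Missing final values are built into the design: participants who abort the intervention are not invited to the final assessment, and the sample size section assumes 20% drop-out. At stake are the credibility and precision of the two balance endpoints. Balance is one of the programme's four training components.

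**Working it through.** **1. The plan's own figure.** The article gives power only for the primary endpoint, from a simulation using this same imputation: 94.6% with 105 per group, and 86.7% if the baseline–final correlation is 0.70. Inputs from Sample size and power calculations: variance 25.09, centre variance 1.59, correlation 0.78, improvements of 2.5 s and 0.5 s, drop-out 20%, α = 0.05. Added assumptions: 15 centres, a two-sided test, 4,000 runs.

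| Correlation | Stated | Centre effect in both times | Centre effect in baseline only |
|---|---|---|---|
| 0.78 | 94.6% | 94.4% | 92.6% |
| 0.70 | 86.7% | 87.3% | 86.2% |

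The stated power reproduces to within 2 points, so the imputation rule is understood as the authors used it.

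**2. The rule on a capped score.** Read for a secondary endpoint, the change drawn is the change on that endpoint. For drop-out *i* and randomly drawn control *j*:

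imputed final value = B_i + D_j, where D_j = (final − baseline) of control *j*.

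With cap M, the value is impossible when D_j > M − B_i, or when D_j < −B_i. At B_i = M, any positive change is enough.

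- Tandem stand: 10 s + 3 s = 13 s on a 10 s test.
- Tandem walk: 8 + 2 = 10 steps on an 8-step test.

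**3. How often.** The documents give no scores for either test, so this step rests on assumption. Latent normal score with SD 4 s, limited to 0–10 s; 20% random drop-out, so 0.20 × 210 = 42 imputed values; control shift 0 or 0.5 s:

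| At cap at baseline | Correlation | Imputed above 10 s | Imputed below 0 s |
|---|---|---|---|
| 31% | 0.50 | 22.9–25.2% | 3.9–4.7% |
| 31% | 0.70 | 20.1–22.7% | 2.7–3.5% |
| 31% | 0.85 | 17.4–20.9% | 1.8–2.4% |
| 50% | 0.70 | 21.0–23.5% | 0.8–1.0% |
| 69% | 0.70 | 16.8–18.7% | 0.1–0.2% |

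At least one value above 10 s appeared in 99.8–100% of simulated trials. A second set of assumptions (SD 3–6, correlation 0.6–0.8, 30–70% at the cap) gave 15–23% for tandem stand and 11–19% of imputed tandem walks above 8 steps. Together, tandem stand is at about 15–25%:

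- of the 42 imputed values: 0.15 × 42 = 6.3 to 0.25 × 42 = 10.5;
- of all analysed values: 0.20 × 15% = 3% to 0.20 × 25% = 5%.

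**4. What it does to the result.** Tandem stand, 105 per group, 15 centres, 20% missing, latent correlation 0.6, SD 4 s, and an assumed latent effect of 2 s, analysed with the planned ANCOVA:

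| At cap | Estimate, unbounded | Estimate, limited to range | Power, unbounded | Power, limited to range |
|---|---|---|---|---|
| about 30% | 0.96 s | 0.94 s | 79% | 85% |
| about 50% | 0.63 s | 0.63 s | 63% | 70% |
| about 70% | 0.35 s | 0.35 s | 44% | 51% |

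The estimates and the powers come from separate simulations of this set-up. The losses in the table are 85 − 79 = 6, 70 − 63 = 7 and 51 − 44 = 7 points; across simulations they were 3–7 points. With no effect, the unbounded rule rejected in 4.3–4.9% of runs, close to the nominal 5%.

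**The case against.** The best defence is that the article is a condensation. It words the imputation for chair-rise time only and extends it in one generic sentence, and adapting it to each instrument could be left to an analysis plan that is not shown. This limits the seriousness but does not remove the point. The article does not leave the rule open: it fixes one rule for all secondary endpoints and names a single exception, which concerns missing baselines. Followed as written, it produces out-of-range scores.

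A second defence is that the consequence is small. That stands: the estimate and the type I error hardly move.

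A reader might infer more than this from the text:

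- **That capped scores make ANCOVA unsuitable.** The documents do not support this. Continuous can fairly be read as numeric rather than categorical, which is how the article also labels chair-rise time. The difference in mean seconds held on a 10 s test is a legitimate quantity, and the test kept its level. A ceiling does shrink an effect relative to a latent scale, but it comes from the test itself, and no model recovers information above it.
- **That an ordinal model is required.** Collapsing the scores to failed, partial and maximum discards information below the cap. It would also need about 15 centre terms with about 14 patients per centre, where sparse cells are likely. That is a trade-off and not a correction.
- **That imputed stands of up to 20 s are to be expected.** That needs a recipient at 10 s and a control who went from 0 to 10 s. It is possible but extreme.

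**Conclusion.** The rule as written is wrong for tandem stand and tandem walk, and the issue is minor. That it can yield scores above 10 s or 8 steps follows from the text by simple addition; it would yield none only if no drawn change exceeded the recipient's room to the cap. The frequency (15–25% of imputed tandem stands, 3–5% of all analysed values) and the cost (3–7 points of power on tandem stand) rest on assumed latent-normal scores with 30–70% at the cap and 20% random drop-out. The power cost also assumes a 2 s latent effect. Values below zero are the least stable part: near 0% when most participants are at the cap, and up to about 11% under the least favourable assumptions tried. No material bias or loss of type I error control was found. Chair-rise time has no stated upper cap, so the primary analysis and the powers of 94.6% and 86.7% are unaffected.

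**What to change.** Add one sentence to the rule for secondary endpoints: for tandem stand and tandem walk, imputed final values stay within 0–10 s and 0–8 steps. Two ways are adequate, and one should be named in advance:

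- truncate baseline plus drawn change at the limits of the test; or
- draw the final value itself from controls with a similar baseline score, which keeps it in range by construction but may leave few donors in some baseline groups.

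Qualify the statement that all secondary measures are continuous by noting that these two are bounded. Keep the ANCOVA as planned. An ordinal model may be added as an optional sensitivity analysis for the ceiling.

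The cost is a sentence or two of wording and a line of code. No new data are needed, and neither the sample size nor the primary analysis changes.

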#### Patient compliance

Attendance at consultations (at the GP's practice and on the telephone) is documented by the exercise therapists as measure of patient compliance (paper protocols).

#### Appraisal by participants

During the final telephone interview, participants who completed the intervention are asked to rate the programme (standardised questionnaire). The rating (on a scale) includes quality, content and frequency of programme actions (e.g. personal and telephone exercise consultations) as well as quality and content of materials (e.g. workbook). Additionally, participants are asked to rate the concept used to approach and support them through their GP's practice.

#### Appraisal by GPs

After completion of the intervention within their practice, GPs are asked to rate the programme (standardised questionnaire on paper protocol). The rating (on a scale) mainly refers to the GPs' perception about their effort expended with and their benefit derived from the programme.

#### Appraisal by exercise therapists

After completion of all interventions, exercise therapists are invited to take part in a focus group discussion to share their opinion and experiences concerning the additional training programme for the HOMEfit study as well as the design, the content and the practical application of the HOMEfit programme.

#### (Serious) adverse events

During every encounter with the participant (either experimental or control intervention group), the exercise therapist assesses and documents all adverse events (AEs, any previously unknown or increasing symptom or disease of any participant) by a standardised report protocol. The therapist forwards all protocols with AEs (the same day, personally or via fax) to the GP, who judges: serious/not serious; related/not related to participation in the study; subject may not continue participation/subject may continue participation but has to pause completely for x days/subject may continue participation immediately but with restrictions for x days/subject may continue participation immediately without any restrictions. Adapting the ICH Guidelines on "Clinical Safety Data Management-Definitions and Standards for Expedited Reporting E2A" [112] to our intervention, a serious adverse event (SAE) is defined as "any untoward medical occurrence that [...] results in death, is life-threatening, requires inpatient hospitalisation [...]" or "results in persistent or significant disability/incapacity [...]".

Outcome assessors report SAEs to the GP on the same day, if they obtain the information during assessments at the practice.

SAEs are also independently reported by the GP using the standardised report protocol immediately after he/she obtains knowledge of them during routine consultations at the practice or via other information routes.

Protocols of adverse events that have been classified as "serious" by the GP are forwarded promptly by fax (secure receipt) to the SAE manager (who is affiliated to the Institute of General Practice and Family Medicine, University of Witten/Herdecke), who reviews the GP's judgements. AE protocols remain at the practice for monitoring purpose.

The Institute of General Practice and Family Medicine (University of Witten/Herdecke) collects all SAE protocols, analyses frequency and type of SAEs and provides summary reports to the Data Safety and Monitoring Board (DSMB) on a regular basis. In case of numerous occurrences of SAEs, the DSMB suggests that the study should be stopped.

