#### Reasons for discontinued intervention

For future report in the CONSORT flow diagram [113], medical as well as non-medical reasons for discontinued participation (if applicable) are documented by the exercise therapist (paper protocol). For every participant, this documentation starts with the date on which written informed consent is given. Participants who temporarily or ultimately discontinue the participation voluntarily are asked to give a personal reason (voluntary response) by their therapist, either during a personal encounter or by telephone.

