##### Patient compliance, appraisal by participants and by GPs, (S)AEs, discontinued participation

Patient compliance, appraisal by participants and by GPs, (S)AEs, and discontinued participation are analysed descriptively and presented per group (experimental vs. control).

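### Active collection of non-serious adverse events ends when a participant aborts, and the per-group AE summary states no allowance for the shorter observation

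*Protocol article*

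**What the plan says.** The section *(Serious) adverse events* of the protocol article sets out three reporting routes.

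- **Exercise therapist, all AEs.** "During every encounter with the participant (either experimental or control intervention group), the exercise therapist assesses and documents all adverse events".
- **Outcome assessors, SAEs only.** "Outcome assessors report SAEs to the GP on the same day, if they obtain the information during assessments at the practice".
- **GP, SAEs only.** "SAEs are also independently reported by the GP using the standardised report protocol immediately after he/she obtains knowledge of them", the knowledge coming "during routine consultations at the practice or via other information routes".

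Under *Statistical analyses, Primary efficacy endpoint*: "Participants who abort the intervention are not invited for the final assessment". Under *Reasons for discontinued intervention*, participants who stop voluntarily "are asked to give a personal reason (voluntary response) by their therapist, either during a personal encounter or by telephone". The safety analysis is a single sentence, in the last part of *Statistical analyses*: "S)AEs, and discontinued participation are analysed descriptively and presented per group".

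Therapist contacts fall in weeks 1, 2, 4, 5, 7, 8, 11 and 12, with the same number in both arms (*Experimental and control intervention, Overview* and *Common aspects for both groups*).

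**The concern.** Efficacy is analysed by intention to treat, but active safety collection is tied to staying in the programme. Three features of the document make the gap likely to matter.

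- An AE report can itself end participation, because one of the judgements open to the GP is that the person must leave. For that participant, an AE closes the route by which later AEs would be recorded.
- *Ethical considerations and ethical approval* accepts that exercise may at first raise the risk of musculoskeletal injury. Many such injuries would not meet the SAE definition, so they depend on the therapist route alone. No efficacy endpoint counts falls or injuries after randomisation.
- Therapist contacts are up to three weeks apart (weeks 8 to 11). Someone who stops between contacts because of symptoms may be reached only by the request for a reason. That answer is voluntary and is filed as a discontinuation reason; the text does not say that the AE report form is used.

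At stake is the comparison of non-serious AEs between an exercise programme and light-activity advice. If one arm loses more people, or loses them earlier, it is watched for less time and can look safer than it is.

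**Working it through.** **Plan's own figure.** The article states no figure for AE capture. The only calculated figure that uses drop-out is the power in *Sample size and power calculations*. Simulating that ANCOVA (15 centres, two-sided 0.05, 6,000 runs) with 20% drop-out in both arms gives 94.7% against the stated 94.6% at correlation 0.78, and 86.7% against 86.7% at correlation 0.7. Reading the 20% as equal in both arms is thus consistent with the plan's own result.

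**Which routes remain after an abort**

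| Route | Non-serious AEs | SAEs |
|---|---|---|
| Therapist encounter | ends, apart from a possible contact at discontinuation | same |
| Outcome assessor at final assessment | never a stated route | lost, because aborters are not invited |
| GP | never a stated route | continues, but passively |

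**Size of the effect on non-serious AEs.** Let *d* be the abort rate in an arm and *f* the share of the 12 weeks during which an aborter is observed. With a constant AE rate:

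capture in an arm = 1 − *d* × (1 − *f*)

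With the same true rate in both arms, the ratio of recorded AEs is the ratio of the two captures.

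Values of *f* (assumptions; the article gives no abort times):

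- *f* = 1/2: aborts spread evenly over 12 weeks, with AEs picked up at a discontinuation contact.
- *f* = 0.424: aborts spread evenly, AEs known only up to the last scheduled encounter. The mean last encounter is (0×1 + 1×1 + 2×2 + 4×1 + 5×2 + 7×1 + 8×3 + 11×1)/12 = 61/12 = 5.08 weeks, and 5.08/12 = 0.424.
- *f* = 1/3: observation ends at week 4.
- *f* = 1/4: observation ends at week 3 on average.

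Abort rates: 20% in both arms (the plan's drop-out figure), then 25% vs 15% and 30% vs 10% (assumptions with the same 20% average).

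| *f* | 20% vs 20% | 25% vs 15% | 30% vs 10% |
|---|---|---|---|
| 1/2 | 0.900/0.900 = 1.00 | 0.875/0.925 = 0.946 | 0.850/0.950 = 0.895 |
| 0.424 | 0.885/0.885 = 1.00 | 0.856/0.914 = 0.937 | 0.827/0.942 = 0.878 |
| 1/3 | 0.867/0.867 = 1.00 | 0.833/0.900 = 0.926 | 0.800/0.933 = 0.857 |
| 1/4 | 0.850/0.850 = 1.00 | 0.8125/0.8875 = 0.915 | 0.775/0.925 = 0.838 |

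For *f* from 1/2 to 1/3, the arm with more aborts shows 5–7% fewer non-serious AEs at 25% vs 15%; at *f* = 1/4 it shows 8% fewer. At 30% vs 10% the shortfall runs from 10.5% (*f* = 1/2) to 16.2% (*f* = 1/4).

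With equal aborts the ratio is 1.00, but each arm still lacks active AE collection for 10% (*f* = 1/2) to 15% (*f* = 1/4) of its person-time.

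**Effect of a rate.** Under the same assumptions, dividing each arm's count by its observed person-time cancels the capture factor and restores a ratio of 1.00. It does not recover events that happen after an abort, so it cannot replace continued collection.

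**The case against.** A reader might infer that all safety observation stops at abort. The text does not support that. The GP reports SAEs independently of the therapist, and nothing ends this duty when the intervention stops. Participants are the GP's own patients and are assured of unchanged care if they discontinue. What remains true is that this route is passive and covers SAEs only.

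It is also tempting to blame the missing final assessment for the gap in non-serious AEs. Assessors are not stated to record non-serious AEs for anyone, so the missing visit costs only a possible SAE report.

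Events that lead to stopping do have routes: AEs found at an encounter are documented and judged by the GP, medical reasons for stopping are recorded, and the contact at discontinuation may count as an encounter. This narrows the loss mainly to non-serious events arising after the programme has stopped, or between the last contact and the stop. The *f* = 1/2 row already credits such a contact.

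A reader might conclude that the AE table will be biased between arms. The article assumes a single 20% drop-out rate and the same contact schedule in both arms, and with equal abort rates and timing there is no between-arm distortion.

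The choice between counts and rates can fairly be left to an analysis plan. The article does not rule out exposure time, and discontinuation is reported by arm in the same sentence, so an imbalance in numbers would be visible. The rate is therefore a recommendation and not the correction of an error. The collection rule is different, because the article itself fixes who records which events and when.

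Finally, the per-group summary is not the trial's only safety information: SAE frequency and type are analysed separately and reported to the DSMB.

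**Conclusion.** The concern holds for non-serious AEs and for active ascertainment of SAEs. As written, active AE collection ends at abort, SAE capture continues only through what the GP happens to learn, and the per-group presentation states no allowance for unequal observation.

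Any distortion between arms is conditional on abort rates or timing differing. Under a constant AE rate that is equal in both arms, it is about 5–7% fewer recorded non-serious AEs at 25% vs 15% aborts (8% at the earliest timing considered) and about 10–16% fewer at 30% vs 10%. Neither split comes from the document. If people who abort have more events than others, the loss is larger; if events become rarer once exercise stops, it is smaller. None of these percentages should be applied to SAEs, whose GP route stays open.

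**What to change.** In *(Serious) adverse events*, state that AEs and SAEs are collected to week 12 for every randomised participant who agrees, whether or not the intervention continues. For those who have stopped, use one telephone contact at week 12 by the existing blinded interviewers, with the standard report form.

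In the safety paragraph of *Statistical analyses*, present AEs by arm together with observed person-time, as AEs per person-week. The recorded contact dates supply the person-time.

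The cost is about 20% × 210 = 42 short calls and one analysis line. Some who withdrew will decline, so the gap shrinks but does not close; the person-time figure shows what remains. The change affects data collection and reporting only, and leaves the rules for stopping or continuing the intervention as they are.
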